### Randomization and blinding

When the baseline questionnaires and the sleep diary are completed, the participants are randomized. Randomization is computer generated, by the webbased system (CastorEdc). Block randomization (blocks of 2 or 4) will be used to create similar distributions in the different study arms. Randomization into the two treatment groups is at patient level and will be stratified by benzodiazepine use, at least once every 2 weeks (i.e., no *versus* benzodiazepine use) at baseline and by referral type (self-referral versus referral by health care worker). Randomization will be executed centrally by a researcher/assistant who is not involved in the recruitment and inclusion of patients.

The research assistant informs the participants by phone about the result of the randomization procedure and explains the CBT-I appointment or how to collect the medication at the hospital pharmacy. The coordinating researcher and participant agree upon and document the date on which the participant will start taking/attending the study treatment.

It is not possible to blind participants or therapists to allocation; statistical analysis will be conducted by an independent statistician who will be blinded for group allocation.

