## Interventions

### Medication

The treatment regime for the low dose of AM mimics current off-label practice as much as possible, i.e., a 12-week period of 10 mg AM, with the possibility of doubling the dosages by patients themselves at approximately 3 weeks, and medication stop at 12 weeks. Furthermore, participants who opt for a double dosage regime are allowed to return to a single dosage regime within the 12 week treatment. The participants in the AM group have a consultation with a neurologist at least once during treatment at approximately 6 weeks and at 12 weeks to evaluate the effect, dosage, and side-effects of treatment and guide medication stop. At the 6 weeks consultation, participants who doubled their dose to 20 mg at 3 weeks and wish to continue this double dose up to 12 weeks will receive prescription for a second badge AM as one badge AM is only sufficient for a single dose for 12 weeks. The neurologist inquires and motivates the adherence to medication during the appointment at 6 weeks after start of treatment. At the 12 weeks consultation, the neurologists motivate and guide medication stop.

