### Concomitant care during the trial

Subjects in the AM treatment group are advised to refrain from activities that require attention such as car driving when using AM in the first week. The use of other medication including benzodiazepines is allowed during participation in the trial. The only exception is the use of other psychopharmaceuticals. The general practitioner and the pharmacy of the patient is informed about study participation so that new prescriptions are checked for potential drug-drug interactions. Patients are instructed to refrain from using over-the-counter treatments as much as possible. We will monitor the use of both prescribed and over-the-counter sleep medication by questionnaire.

During the treatment period, all patients have access to written or online sleep hygiene advices provided by the participating hospital. In case of acute worsening of the insomnia due to a life-event or a comparable situation, other treatments might be prescribed by a medical doctor (such as benzodiazepines). This use will be monitored by self-report from the patient. Participants are instructed to report new or an increase of existing symptoms during the study to the clinician or researcher.

Adverse events will be treated and followed by the medical specialist conform usual practice. Participants who do not respond or relapse during the study or who request to end study participation will be invited to an individual follow-up session and offered further treatment outside the context of the study if required. The investigator and the treating physician in consultation with the research team can decide to withdraw a participant from the study for urgent medical reasons which are not predefined. The treatment can also be stopped at request of the patient. Those patients who choose to discontinue the treatment are offered the other treatment outside the context of the study.

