### Outcome measures

Primary outcome is insomnia severity measured with the Insomnia Severity Index (ISI) [41] after 12 weeks of treatment. The ISI is a 7-item questionnaire scored on a 5-point Likert scale reflecting the severity of both nighttime and daytime aspects of insomnia disorder as perceived by the participant in the last 2 weeks. Total scores range from 0 (no insomnia) to 28 (severe insomnia). A score of ≥ 10 is used to define clinical insomnia [44] .

We will use the Consensus sleep diary [45] for 1 week. Several variables will be calculated from the sleep diary: sleep efficiency (SE; percentage of time slept from the total amount of time spent in bed), sleep onset latency (SOL; time it takes to first fall asleep), number of awakenings (NOA), and total sleep time (TST, total number of hours the participant has slept). All these estimates are registered for 7 nights and for each variable a mean score over 7 days will be calculated.

Fatigue will be assessed with the subscale Fatigue severity of the Checklist Individual Strength (CIS-20), indicating the level of fatigue in the previous 2 weeks, measured with 8 items on a seven-point scale (range 8–56). A score of 35 or higher on the subscale indicates severe fatigue [46].

Anxiety and depression will be assessed with the Hospital Anxiety and Depression Scale (HADS) [47, 48], which has been extensively used in patients with medical conditions. The HADS contains 14 items (7 on depression and 7 on anxiety). A total score (range of 0–21) for each subscale is computed.

Pain severity and impact of pain on functioning will be measured with the 2-item subscale Bodily pain of the Short-Form 36-item Health Survey (SF-36) [49]. A total score is calculated ranging from 0 to 100. Higher scores indicate less pain and less impact of pain on functioning [50].

Impairment of functioning is assessed with the Work and Social Adjustment Scale (WSAS) [51]. The WSAS assesses five domains of functioning (work, home management, social leisure activities, private leisure activities, close relationships) with one item each. Each item is scored on an 8-point Likert scale. The usual timeframe (1 year) is adjusted to the past 2 weeks.

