The primary analysis will be conducted according to intention-to-treat, i.e., all randomized patients are included and are analyzed in their randomly assigned treatment group. We will use multiple imputations to handle missing data for outcomes that are based on the measurement at a single time point, including the primary outcome of the ISI score at week 12. We will include all baseline demographic and clinical characteristics in the imputation model. We will impute a total of five datasets and these will be pooled according to Rubin’s rule [63].

Additionally, the mean ISI score over time will be compared between the two treatment groups using linear mixed models with treatment group (amitriptyline or CBT-I) and time (6 and 12 weeks from baseline) included as fixed effects and ISI score at baseline included as covariate.

We will repeat the ANCOVA and the linear mixed models analysis of the ISI score as a per protocol analysis in which only patients who actually received their assigned treatment (in the CBT-I group attendance of at least 5 out of 7 sessions and in the AM group at least 70 out of 84 days medication) will be included.

Percentages responders until relapse at 2, 4, 6, 8, 10, and 12 months post treatment in both treatment groups will be compared using survival analyses. We will express the difference between amitriptyline and CBT-I in effect sizes and percentage responders. Treatment response is defined as ≥ 8 point reduction on ISI. A relapse is defined as a drawback of ≤ 8 points to the baseline score of the Insomnia Severity Index measured during follow-up at two subsequent measurements.

ANCOVA will be repeated on the secondary outcome measures assessed at week 12 and 12 months, adjusted for the baseline measurement and the linear mixed models will be repeated for the secondary outcomes sleep quality, fatigue, emotional complaints, physical functioning, impairment of functioning, and pain, all assessed at weeks 6 and 12 and 12 months post treatment adjusted for the baseline measurement, according to intention to treat and per protocol analyses. Bonferroni corrections will be applied to the p-values to account for multiple comparisons.

Rates of reported side effects, withdrawal, and rebound symptoms as well as the treatment evaluation items will be described.

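### The relapse rule ignores insomnia treatment after week 12, so responders treated before relapse is confirmed, or kept on amitriptyline, count as sustained responders

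*Protocol article*

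**What the plan says.** Relapse up to 12 months after treatment is the first item under Secondary objective. The Statistical analysis section defines response as an ISI reduction of at least 8 points. Relapse is a fall back to no more than 8 points from baseline on the "Insomnia Severity Index measured during follow-up at two subsequent measurements". Responders are compared until relapse at months 2, 4, 6, 8, 10 and 12 by survival analyses. The ISI rates symptoms "as perceived by the participant in the last 2 weeks" (Outcome measures).

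Three other sections bear on treatment after week 12:

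- **Concomitant care during the trial:** "The use of other medication including benzodiazepines is allowed during participation in the trial", with other psychopharmaceuticals as the exception. Participants who relapse or do not respond are invited to an individual session and offered further treatment outside the study if needed. Also, "Those patients who choose to discontinue the treatment are offered the other treatment outside the context of the study". On recording: "We will monitor the use of both prescribed and over-the-counter sleep medication by questionnaire".
- **Medication:** the course ends at 12 weeks, and "At the 12 weeks consultation, the neurologists motivate and guide medication stop".
- **Additional measures:** prescriptions are taken from the patient file for the year after randomisation, whereas follow-up runs to 15 months (Methods/design).

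Randomisation is "stratified by benzodiazepine use, at least once every 2 weeks" at baseline.

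**The concern.** The rule looks only at the ISI, and the ISI shows how the patient is doing under whatever is being taken at the time. The same article makes treatment available when insomnia returns. So a patient whose response has been lost can be restored by treatment and still count as a lasting success.

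This matters because durability is where the two treatments are most likely to part. The Background gives higher relapse after benzodiazepine receptor agonists are stopped as the reason for the stronger long-term support for CBT-I. Readers will ask the same question of amitriptyline. The trial is open-label and one arm loses its drug at week 12, so unequal later treatment is plausible. Stratification balances benzodiazepine use at entry and does nothing about new or increased use later.

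**Working it through.** **1. No plan figure to reproduce.** The article states no relapse rate, event count or power for relapse. The 84 per group under Sample size belongs to the week-12 comparison and serves below only as a head count.

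**2. Three responders under the rule**, read as a score within 8 points of baseline at two successive two-monthly visits:

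- A worsens to within 8 points, receives no treatment and is still there at the next visit: relapse.
- B worsens in the same way, starts a hypnotic and is more than 8 points below baseline at the next visit: no relapse.
- C continues amitriptyline after week 12 and stays more than 8 points below baseline: no relapse.

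A and B lost response alike and differ only in being treated. C's response off the drug is never observed.

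**3. Effect on relapse percentages (all inputs assumed).** Let p be the true relapse proportion, s the share of relapsers treated before confirmation, and w = 0.7 the chance that treatment works. Observed relapse = p × (1 − s × w).

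| True, AM / CBT-I | Treated, AM / CBT-I | Observed, AM / CBT-I | Difference (points) |
|---|---|---|---|
| 50% / 30% | 30% / 30% | 39.5% / 23.7% | 15.8 (true 20) |
| 50% / 30% | 50% / 20% | 32.5% / 25.8% | 6.7 (true 20) |
| 50% / 30% | 70% / 20% | 25.5% / 25.8% | −0.3 (true 20) |
| 40% / 40% | 30% / 30% | 31.6% / 31.6% | 0 (true 0) |
| 40% / 40% | 50% / 20% | 26.0% / 34.4% | −8.4 (true 0) |

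For example, 0.50 × (1 − 0.50 × 0.7) = 0.325. In the 40% / 40% case, swapping the treated shares reverses the sign. Counting treatment as an event restores the true difference here, but only because every treated patient in this example is a true relapser.

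**4. The same in patients.** The Background says CBT-I improves sleep in about 70–80%. Assume that this holds for the 8-point response and in both arms: 84 × 0.70 = 59 and 84 × 0.80 = 67 responders per arm.

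- One hidden relapse moves an arm's percentage by 1/67 = 1.5 to 1/59 = 1.7 points.
- An excess of 3 to 6 in one arm moves the difference by 3/67 = 4.5 to 6/59 = 10.2 points.
- Standard error of the difference at an assumed 30% relapse: √(2 × 0.3 × 0.7/67) = 7.9 to √(2 × 0.3 × 0.7/59) = 8.4 points.
- Apparent hazard ratio with no true difference, ln(1 − p1)/ln(1 − p2): 17/67 v 20/67 gives 0.83; 12/59 v 18/59 gives 0.62. The inverses are 1.21 and 1.60.

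**5. Overlap at 8 points.** A reduction of exactly 8 meets both definitions, so a patient who stays there is a responder and then relapsed without changing. With a rounded-normal reduction of mean m and SD d, the share of responders at exactly 8 is [Φ((8.5 − m)/d) − Φ((7.5 − m)/d)] / [1 − Φ((7.5 − m)/d)]. For assumed m = 6 to 10 and d = 4.4 to 6.5 this runs from 9% (m = 10, d = 6.5) to 22% (m = 6, d = 4.4).

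**6. Month 12.** A first qualifying score at the last visit cannot be confirmed. If relapse is dated at the first score, then under constant hazard and an assumed 20–40% relapse this affects (0.80^(10/12) − 0.80)/0.20 = 15% to (0.60^(10/12) − 0.60)/0.40 = 13% of relapses. It lowers both arms and leaves the hazard ratio essentially unchanged.

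**7. Data coverage.** Treatment takes about 3 of the 12 months after randomisation, so the file extraction covers about 9 of the 12 post-treatment months.

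**The case against.** The strongest reply is that scoring the ISI regardless of later treatment is a treatment-policy approach. It fits the intention-to-treat analysis, and supplementary analyses are usually left to an analysis plan that is not shown. The first part stands: the approach is legitimate for the question it answers. The second part does not dispose of the point, because the rule is stated in the article beside a care pathway that treats the patients whose relapse it is meant to detect.

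A reader might infer that the trial cannot tell lasting response from response under later treatment. The documents do not support that. Sleep medication is monitored by questionnaire and prescriptions are extracted; the stated relapse analysis simply makes no use of them, and the file data stop three months early.

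The care section can also be over-read. The sentence on prescribing for acute worsening sits in a paragraph about the treatment period. The offer of the other treatment goes to people who stop their course. Both say little about responders after week 12. The weight rests on the allowance of benzodiazepines throughout, the offer to participants who relapse and the guided stop. If that offer came only after a confirmed ISI relapse, it would hide nothing, but the article does not say so. Continued amitriptyline may also fall under the psychopharmaceutical exception; even so, it would not count as an event.

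The sizes above are assumed, and even 10.2 points lies inside a 95% half-width of 1.96 × 7.9 = 15.5 to 1.96 × 8.4 = 16.5 points. That is fair, and is why no size is claimed.

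**Conclusion.** The point holds for the relapse comparison only. The stated rule counts some treated relapses and any successful continued amitriptyline use as sustained response. The bias depends on how later treatment differs between arms. A reader might infer that it favours amitriptyline; nothing in the document fixes the direction, and the size cannot be derived from it. Equal hidden numbers leave no bias when there is no true difference, though equal treated shares can shrink a real difference in percentage points, as in the first table row.

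A reader might also infer that the rule is otherwise sound. It should not be called defensible while response and relapse overlap at exactly 8 points. This rests on reading the relapse wording as a score within 8 points of baseline. The month-12 gap is minor. The week-12 non-inferiority analysis is untouched.

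**What to change.** 1. Pre-specify a supplementary relapse analysis in which starting, resuming or increasing insomnia treatment after week 12 (a hypnotic, amitriptyline or the other arm's treatment) is a relapse event. Date it at the change, or at the visit where it is first reported if no date is recorded.
2. Show continued amitriptyline as a separate variant, since it can occur in only one arm.
3. Handle an unconfirmed month-12 score in its own analysis, so that any change in the result can be attributed.
4. Report insomnia treatment after week 12 by arm from the planned questionnaire, and extend the prescription extraction from 12 to 15 months after randomisation.
5. Reword relapse so that it cannot be met by a patient who still meets the response criterion, for example a score less than 8 points below baseline.

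The cost is a few added analyses on data mostly already planned and three more months of record extraction; visits and care do not change. There are two downsides. The composite will include some prescribing for life events, and the continued-amitriptyline variant is asymmetric against amitriptyline. Both should be stated with the results.

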### Statistical analysis

Demographic and clinical characteristics (e.g., age, gender, medical condition, preference and type of insomnia) and primary and secondary outcomes at baseline (e.g., sleep efficiency, emotional complaints) will be presented in means (standard deviations) and numbers (percentages) depending on their distribution.

The null hypothesis states that there is a difference in mean scores on the primary outcome between the treatment groups; the alternative hypothesis is that the difference in mean scores on the primary outcome measure does not differ by more than the non-inferiority margin. The primary analysis will be conducted according to intention-to-treat, i.e., all randomized patients are included and are analyzed in their randomly assigned treatment group. Outcomes that are based on measurements at multiple time points, i.e., weeks 6 and 12, are analyzed using mixed linear models. Mixed linear models can handle the presence of missing data without the need for imputation and still provide valid estimates of treatment effects.

The primary outcome for analysis is the mean subjective insomnia severity as assessed using the ISI at week 12. To test for the difference between the two treatment groups, the primary outcome of ISI score at week 12 will be analyzed using analysis of covariance (ANCOVA) with treatment group (amitriptyline or CBT-I) as the independent variable and the baseline value as a covariate. We will check for violations of necessary assumptions of ANCOVA (normality, homogeneity of variance and random independent samples). We will calculate a one-sided 95% confidence interval around the mean difference in the primary outcome between the treatment groups to determine if the upper limit of the confidence interval will be below the non-inferiority margin of 4 points. Amitriptyline will be declared non-inferior to CBT-I if the upper bound of the 95% confidence interval does not exceed the non-inferiority margin of 4 points. If amitriptyline is shown to be non-inferior, we then will proceed to superiority hypothesis testing. For superiority testing, we will consider the two sided 95% confidence interval of the mean difference between both groups on the primary outcome as established in the ANCOVA and verify if it includes zero or not.

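### Secondary outcomes are tested on the same data by two models and in two populations with none named as deciding, and plain Bonferroni spends alpha on the repeats

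*Protocol article*

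**What the plan says.** All of this is in the Statistical analysis section of the protocol article unless another section is named.

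- First model: "ANCOVA will be repeated on the secondary outcome measures assessed at week 12 and 12 months, adjusted for the baseline measurement".
- Second model, in the same sentence: "linear mixed models will be repeated for the secondary outcomes sleep quality, fatigue, emotional complaints, physical functioning, impairment of functioning, and pain". Its time points and populations are given as follows: "all assessed at weeks 6 and 12 and 12 months post treatment adjusted for the baseline measurement, according to intention to treat and per protocol".
- Multiplicity: "Bonferroni corrections will be applied to the p-values to account for multiple comparisons". The sentence gives neither the family nor the divisor.
- General rule earlier in the section: "Outcomes that are based on measurements at multiple time points, i.e., weeks 6 and 12, are analyzed using mixed linear models". By that rule the repeatedly measured secondary outcomes belong to the mixed model, yet ANCOVA is added for them.
- Population: "The primary analysis will be conducted according to intention-to-treat, i.e., all randomized patients are included and are analyzed in their randomly assigned treatment group". This appears in text about the primary outcome, and per protocol is introduced there as a repeat for the ISI.
- Treated differently: relapse ("Percentages responders until relapse at 2, 4, 6, 8, 10, and 12 months post treatment in both treatment groups will be compared using survival analyses"), while side effects and withdrawal are only described.
- Number of outcomes: under Outcome measures, "Several variables will be calculated from the sleep diary: sleep efficiency" opens a list of four diary variables. Fatigue, anxiety, depression, pain and impairment of functioning follow, which makes nine scored measures. Physical functioning is a named secondary outcome in the Secondary objective and in the Statistical analysis section, but is not among these nine.

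**The concern.** For the primary outcome the plan is clear: ISI at week 12, ANCOVA, intention to treat. The secondary outcomes handled by ANCOVA and mixed models have no such ranking. Each receives several strongly overlapping tests of one question. The two models also treat missing data differently: multiple imputation is prescribed for single-time-point outcomes and no imputation for mixed models. They can therefore disagree about the same week-12 data, and nothing says which result stands.

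Bonferroni is then attached to the p-values. If all of them are counted, most of the alpha goes to repeats that add little independent evidence, and a real moderate difference between the arms is easily missed. If the correction is applied only inside each set of analyses, the chance of at least one false difference exceeds 5%. The Discussion says that results on daytime symptoms should help patients and caregivers choose between the treatments, so either outcome matters.

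**Working it through.** The article gives no power, number of tests or error rate for secondary outcomes, so there is no stated figure to reproduce.

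**Inputs.** From the article: 84 per group (Sample size), used here only as the number analysed; ANCOVA at two time points; mixed models on the same data plus week 6; two populations; nine scored measures. Assumed: standardised differences of 0.5 and 0.4, one treatment test per mixed model, a per-protocol set of 75% of patients, a correlation of 0.5 between visits, and correlations of 0 to 0.7 between outcomes.

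**Count.** 9 outcomes × 3 analyses (ANCOVA week 12, ANCOVA 12 months, mixed model) × 2 populations = 54 tests. Other counts are possible. Six domains × 2 models × 2 time points × 2 populations = 48, and ten outcomes on the same basis give 80.

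**Power per outcome.** With k tests, the two-sided level is 0.05/k. Power is the probability that a noncentral t variable, with 2 × 84 − 2 = 166 degrees of freedom and noncentrality d × √(84/2), exceeds the critical value in absolute size. The noncentrality is 3.240 for d = 0.5 and 2.592 for d = 0.4.

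| k | level | critical t | power, d = 0.5 | power, d = 0.4 |
|---|---|---|---|---|
| 1 | 0.05 | 1.974 | 90% | 73% |
| 9 | 0.0056 | 2.810 | 67% | 42% |
| 48 | 0.0010 | 3.338 | 46% | 23% |
| 54 | 0.0009 | 3.373 | 45% | 22% |
| 80 | 0.0006 | 3.487 | 41% | 19% |

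These use 84 per group throughout. Per-protocol tests would have fewer patients and less power.

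**Family-wise error.** I simulated 200,000 null trials under the assumptions above, taking the mixed-model statistic as the standardised sum of the two visit statistics. The per-protocol and intention-to-treat statistics then correlate at √0.75 = 0.87.

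| correlation between outcomes | 0.05/9 within each analysis set | 0.05/6 within each outcome | 0.05/54 overall |
|---|---|---|---|
| 0 | 15.9% | 22.3% | 3.2% |
| 0.3 | 14.5% | 20.2% | 3.0% |
| 0.5 | 12.1% | 16.9% | 2.6% |
| 0.7 | 9.4% | 13.0% | 2.1% |

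A separate simulation with eight tests per outcome, 6 or 10 outcomes and a wider set of correlations gave 10.3% to 27.4% when only the number of outcomes was corrected for. Across both exercises, correcting over the outcomes alone therefore leaves 9.4/5 = 1.9 to 27.4/5 = 5.5 times the nominal 5%.

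**Holm against Bonferroni over nine tests.** With correlation 0.5 between outcomes and d = 0.5, average power rises from 68% to 79% if all nine effects are real and to 71% if four are. It stays at 68% if only one is. For d = 0.4 with all nine real it rises from 43% to 53%. (The simulation uses a normal statistic, hence 68% here against 67% in the power table.)

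**The case against.** The strongest reply is that a Bonferroni divisor, the family and the ranking of supportive analyses commonly sit in a statistical analysis plan or full protocol. The article is condensed, and the protocol version it cites is not shown. That stands: the missing divisor alone is no finding. What remains is what the article itself fixes, namely duplicate analyses of the same outcomes on an equal footing with plain Bonferroni over them.

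Partial rules also exist. Intention to treat is called primary, and outcomes with several time points are assigned to mixed models. These narrow the gap, but the first is written around the primary outcome and the second is overridden when ANCOVA is added.

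Bonferroni is valid under any dependence, so it is conservative here and not erroneous. That stands too. Taken literally, it controls the error (2.1% to 3.2% above), and its cost is power.

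A reader might infer more than the article supports:

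- That every secondary outcome is affected. Relapse goes to survival analysis, and side effects and withdrawal are only described.
- That the correction more than halves power. At d = 0.5 the ratio to no correction is 45.0/89.7 = 0.50, and no correction is not the sensible comparator. Against a correction over nine, the loss is about a third.
- That the error under the narrow reading has one definite value. It depends on correlations and a per-protocol fraction that are not given.
- That only these two readings exist. Intermediate families are possible.
- That 12-month tests should be demoted. The Secondary objective gives 12 weeks and 12 months equal standing.

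**Conclusion.** The point holds for the secondary outcomes analysed by ANCOVA and mixed models. The article commits to overlapping repeats by model and population, ranks none, and applies plain Bonferroni.

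Under the literal reading, the repeats reduce power from 67% to 45% at d = 0.5 and from 42% to 22% at d = 0.4, relative to one test for each of nine outcomes. This rests on 54 tests and 84 analysed patients per group. Under the narrower reading, the family-wise error is roughly 2 to 5 times 5%. The direction is robust, but the exact figures depend on the assumed counts, effects and correlations.

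The primary conclusion is untouched. The change is worth making because it is cheap, and it settles in advance which secondary result counts.

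**What to change.** In the Statistical analysis section:

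1. Name one intention-to-treat model as deciding for each secondary outcome in this group, including physical functioning, at week 12 and at 12 months. ANCOVA would match the primary analysis, whereas the mixed model would follow the section's own rule for repeated measurements. Either choice resolves the ambiguity.
2. State that the other model and all per-protocol repeats are supportive, reported with confidence intervals and kept outside the family.
3. Replace Bonferroni by Holm over the deciding tests at two-sided 5%. Holm has the same error guarantee and rejects everything that Bonferroni rejects, so it is never less powerful. The gain is small if few effects are real.
4. State whether the 12-month tests share the family with week 12 or form a second one. This is the sponsor's choice, and they should not be demoted by default. With ten outcomes (the nine plus physical functioning), the power formula above gives, for the first Holm step, 65% at d = 0.5 (40% at d = 0.4) with two families of ten. It gives 57% (32%) with one family of twenty. Two families allow up to 2 × 5% = 10% error across both.

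The cost is a few sentences before database lock, with no new data or patients. In return, mixed-model or per-protocol repeats can no longer be claimed as confirmatory, and simultaneous confidence intervals are less simple under Holm than under Bonferroni.
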